**Congratulatory reminder for a mother who is on track**
“Congratulations on completing the Getting Started module of the Moms and Teens program [mom’s name]. You are a superstar! To stay on track, make a plan to complete Module 1 with [teen’s name] by [goal day]! Module 1 will help you and your teen talk about healthy relationships. Need technical support? We want to help! Text back ‘Y’ or call XXX-XXX-XXXX”
**Motivation reminder for a mother that has not logged in**
“Dear [mom’s name], we re-sent the login information for the Moms & Teens program to your email. This fun, convenient, and free research-based program has been shown to benefit moms and teens. Make a plan now to login this week to complete the Getting Started module and begin the program with [teen’s name] so that you can get back on track to finish the program by [goal day]. If you need technical support to login to the program text back ‘Y’ or call XXX-XXX-XXXX!”

Once the recommended six week program completion period is complete, all participants who have not finished the program will be notified via email and text and asked to complete the program before the two week grace period ends.

#### Action Planning

Gollwitzer [22] proposed a model of action phases for goal attainment, which suggests that people will be more likely to achieve a goal (such as completing the eMTSD program) if they create an *action* plan in the form of implementation intentions that “spell out the where, when, and how of goal striving in advance.” Research supports this strategy, with a meta-analysis finding that implementation intentions have a moderate to large positive effect on goal attainment [23]. Drawing from this research, mother participants assigned to receive action planning groups will receive a modified version of the email communication with the program log-in information, including additional instructions directing them to complete a brief *action planning* form administered through the REDCap (Research Electronic Data Capture; Vanderbilt University) web application. The action planning form asks participants to (1) make an individual goal for when they would like to finish the program, (2) create a plan for where and when they will complete the program modules with their teenagers, and (3) complete 3 if-then statements to identify the potential barriers to completion that may arise and how they will overcome them. Mothers will be instructed that they can print or save the form to refer to if they desire.

### Definitions and Assessment of Feasibility and Acceptability

#### Feasibility

In this study, *feasibility* will be assessed both in reference to the research processes and to the eMTSD program; that is, feasibility outcomes provide information that enables us to assess the questions of *can this study be done* and *can this program be done*. Specifically, we define feasibility as the extent to which (1) the study is successfully conducted with respect to recruitment, randomization, delivery of adherence support, retention, and assessment, and (2) the eMTSD program can be successfully conducted by mothers and teenagers [24,25]. Textbox 2 summarizes the key feasibility outcomes and their indicators.

Feasibility outcomes.
**Recruitment rate**
Number of dyads recruited per month
**Enrollment rate**
Percentage of eligible dyads who enroll in the study
**Randomization**
Percentage of enrolled dyads correctly randomized
**Retention rate**
Percentage of enrolled dyads who complete the follow-up survey
**Adherence supports**
Percentage of SMS text messages eligible to be delivered and which are sentPercentage of mothers eligible for action planning who complete a plan
**Data collection**
Percentage of missing data within surveysTime taken to complete surveys
**Program uptake and adherence**
Percentage of participants who log in at least oncePercentage of participants who start the program with their teenagerPercentage of modules completed or pages viewedPercentage of enrolled participants who complete the programAdherence index, comprising the sum of the number of completed modules, number of unique visits to the site, and maximum time between visits [26]Time taken to complete program modulesParticipant report of facilitators of and barriers to engaging with the program, including technical problems accessing or using the website

#### Acceptability

In this study, acceptability will be assessed in reference to the eMTSD program, as well as with respect to adherence support factors (SMS text message reminders and action planning). Drawing from the Theoretical Framework of Acceptability (TFA), we define acceptability as the extent to which mothers and teenagers consider eMTSD to be appropriate based on their cognitive and emotional responses to the intervention [27,28]. The TFA was applied to develop quantitative indicators assessing the acceptability of the eMTSD across each of the 7 component domains proposed by the TFA (affective attitude, burden, ethicality, coherence, opportunity costs, perceived effectiveness, and self-efficacy). Table 2 lists the acceptability outcomes, including their linkages to each TFA domain.

**Table 2 table2:** Acceptability outcomes.

Outcome and domain			Indicator or indicators
**Program acceptability**			
	Affective attitude	I enjoyed doing the module or program^a^ The module or program kept my attention^a^	
	Burden	The module or program was easy to do^a^ The module or program was too long^a^	
	Effectiveness	I learned useful information from the module or program^a^ The program will reduce my teen’s chances of experiencing dating abuse^a^	
	Ethicality	The program covered topics that are important to me^a^	
	Cohesiveness	I understood what the program is trying to do^a^	
	Self-efficacy	I understood how to complete the program^a^	
	Opportunity cost	Doing the program was time well spent^a^	
	Overall^b^	Percentage of participants who report agreement with all acceptability indicators	

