**Adherence support acceptability**			
	Effectiveness	Percentage of participants who report it was helpful to receive text reminders Percentage of participants who report it was helpful to complete an action plan	
	Burden	Percentage of participants who report they received too many SMS text messages	

^a^Program acceptability indicators will be operationalized as the percentage of participants who completed the module or program and agreed or strongly agreed with the indicator statement. Some indicators will be asked both in reference to specific modules and in reference to the program as a whole.

^b^We will also create a continuous program acceptability index score for each mother and teenager by summing across acceptability indicators (range 0-9).

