#### Power

We used the approach described by Lewis et al [29] to determine the sample size for this feasibility and acceptability trial. This approach uses a *traffic light* system to evaluate the progression to the main trial based on a set of a priori criteria. Hypothesis testing for binary feasibility outcomes tests against being in the red zone (unacceptable outcome) based on the expectation of being in the green zone (acceptable outcome). Using this approach, an adequate sample size is that which gives high power (≥80%) to reject being in the *red zone* if the *green zone* holds true.

Three focal feasibility and acceptability outcomes were selected to determine the sample size: (1) enrollment rate, (2) overall program acceptability, (3) teenager program initiations, and (4) program completion rates. The point estimates that will be considered the red zone upper limit (R_ul_) and green zone lower limit (G_ll_) for these outcomes are (1) the proportion of those eligible from those who enroll (R_ul_=0.60 and G_ll_=0.75), (2) the proportion of those who agree or strongly agree that the program is acceptable across all indicators >0.60 (R_ul_=0.55 and G_ll_=0.75), (3) the proportion of those enrolled who initiated the use of the program with their teenager >0.50 (R_ul_=0.50 and G_ll_=0.65), and (4) the proportion of those enrolled who completed the program >0.30 (R_ul_=0.30 and G_ll_=0.50). The null hypothesis test, for which the sample size is calculated, is that the true outcome is not greater than R_ul._

Table 3 shows that a sample size of 100 provides >80% power to reject the null hypothesis across each of the focal feasibility and acceptability outcomes, with an α of .05 and a 1-tailed, 1-sample binomial test based on normal approximation (with continuity correction).

**Table 3 table3:** Power for focal binary feasibility and acceptability outcomes.

Outcome	Red zone upper limit, %	Green zone lower limit, %	Power^a^, %	N^b^
Enrollment rate (percentage of those eligible who enroll)	60	75	80	68
Program acceptability (percentage of those completing the program who agree or strongly that the program is acceptable across all domains)	55	75	80	40
Teenager program initiation rate (percentage of those enrolled who start the program with their teenager)	50	65	80	73
Program completion rate (within group; percentage of those assigned to the group who complete all 6 program modules)	25	50	80	25 (per group; 100 overall)

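### As defined in Table 2, overall program acceptability counts agreement that the program was too long as acceptance, which caps a red/green progression outcome

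*Protocol article*

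**What the plan says.** The relevant text is in Table 2 with its footnotes (Acceptability section) and in the Power section of the protocol article.

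- **The item.** Under Burden, Table 2 lists "The module or program was too long". It carries footnote a, as do the nine favourable statements.
- **The scoring rule.** Footnote a turns each marked indicator into the percentage of completers who "agreed or strongly agreed with the indicator statement". It gives one direction and makes no exception.
- **The composite.** The Overall row is the "Percentage of participants who report agreement with all acceptability indicators".
- **The index.** Footnote b adds a score for each mother and teenager, formed by "summing across acceptability indicators (range 0-9").
- **The use.** The Power section adopts a traffic-light "system to evaluate the progression to the main trial based on a set of a priori criteria". One of its focal outcomes is "the proportion of those who agree or strongly agree that the program is acceptable across all indicators", with limits "R_ul_=0.55 and G_ll_=0.75". Table 3 restates it across all domains, among those who complete the program, and gives N = 40.

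Nothing in the article reverses the direction of the Burden item or excludes it.

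**The concern.** Agreement is favourable for nine indicators and unfavourable for the tenth, yet one agree rule covers all ten and the composite requires all ten. A fully satisfied participant who thought the length was right is therefore counted as not accepting the program. The only people who can count as accepting it are those who liked everything and also found it too long.

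The composite has consequences because it is one of the focal outcomes for progression to a main trial. Scored by its stated definition, a well-liked program of suitable length would fall in the red zone. If the definition is instead repaired informally at analysis, the repair is chosen with results in view, and the candidate repairs can put the same data in different zones.

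The index adds a second uncertainty: its stated maximum is one less than the number of listed indicators.

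**Working it through.** **1. The plan's own sample size.** Inputs from the Power section and Table 3: p0 = 0.55, p1 = 0.75, power 80%, and a test "with an α of .05 and a 1-tailed, 1-sample binomial test based on normal approximation (with continuity correction").

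- Uncorrected: n = [(1.645·√(0.55·0.45) + 0.842·√(0.75·0.25)) / 0.20]² = 34.97.
- Continuity-corrected: n/4 · [1 + √(1 + 2/(n·0.20))]² = 39.8, rounded up to **40**.

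This reproduces Table 3; approximate power at 40 is 80.2%. As an exact binomial check, the smallest count that rejects the red zone at n = 40 is 28 (70%), with α = 0.0386 and power 0.821.

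**2. Indicator count.** By domain in Table 2: affective attitude 2, burden 2, effectiveness 2, ethicality 1, cohesiveness 1, self-efficacy 1, opportunity cost 1. The sum is 10. With one point per agreed indicator, ten items give 0-10 and nine give 0-9.

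**3. Upper bound on the composite as written.** Let A be agreement with all nine favourable items and B agreement that the program was too long. The composite is P(A and B), which cannot exceed P(B). This needs no assumption about response rates. Even if every completer endorsed all nine favourable items:

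- the rate equals the red limit only when 55% of completers call the program too long;
- it equals the green limit only when 75% do;
- at n = 40, the exact test rejects the red zone only if at least 28 completers (70%) do.

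**4. Illustration at the green limit.** The article gives no expected response rate for this item, so the following is assumed. Let 75% of completers endorse all nine favourable items, and let a share q of those also agree it was too long. The composite as written is 0.75·q.

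| q | Rate as written | Exact chance of at least 28/40 |
|---|---|---|
| 0.10 | 7.5% | 7.2 × 10⁻²³ |
| 0.20 | 15% | 7.3 × 10⁻¹⁵ |
| 0.50 | 37.5% | 0.00003 |
| 0.80 | 60% | 0.129 |
| 1.00 | 75% | 0.821 |

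The planned power is recovered only when everyone who likes the program also finds it too long. Reaching even 55% needs q = 0.55/0.75 = 0.733.

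**5. The repairs are not equivalent.** Assume 80% endorse all nine favourable items, 20% of those say too long, and the rest of them disagree.

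- As written: 0.80 × 0.20 = 16% (red).
- Reverse-scored: 0.80 × 0.80 = 64% (between the limits).
- Item excluded: 80% (green).

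**The case against.** The strongest reply is that the intended direction is obvious. The item sits under Burden, acceptability is defined as finding the program appropriate, and the Power section and Table 3 speak of the program being acceptable rather than of endorsing each statement. Reverse-coding a negatively worded item is also a detail that a journal article often leaves to the full protocol or analysis plan. Item-level responses are collected in any case, so the right score can be computed later.

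Much of this stands as evidence of intent. It does not cure the text. The article is not silent: footnote a states a direction and is attached to this item, and the Power section still refers to all indicators. Nor does clear intent choose between reversing and excluding the item, which step 5 shows can matter.

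Three stronger readings are tempting and are not supported:

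- *That the index adds the too-long item in the wrong direction, so that 0-10 is the correct range.* A 0-9 range with ten listed items suggests that one item is left out, and the only negatively worded one is a natural candidate. Footnote a also says that only some indicators are asked at both module and program level, so the index's item set is not fully shown. The documents establish a mismatch, not which reading is right.
- *That the trial will report something like 16% instead of 64%.* Those figures follow from assumed response rates and from mechanical use of the footnote.
- *That the sample size is wrong.* N = 40 reproduces.

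The item on receiving too many text messages is a separate adherence-support outcome, outside this composite.

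**Conclusion.** The definition is wrong as written. Under footnote a and the Overall row, agreement with an unfavourable statement is required for acceptance, so the composite is bounded above by the share of completers who call the program too long. That bound follows from the definition alone. How far an observed rate would fall below a sensibly scored one depends on response rates that the article does not give, so the figures in steps 4 and 5 show a range and are not forecasts.

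The mismatch between ten indicators and a 0-9 index is a separate inconsistency: one item appears to be omitted, but neither the item nor its status in Overall is stated. Because the composite feeds a progression decision, both points should be settled before data are analysed.

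**What to change.** State one of the following in Table 2, footnotes a and b:

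1. The too-long item is reverse-scored: acceptable means disagree or strongly disagree. Overall then uses ten items and the index runs 0-10.
2. The too-long item is excluded from the composite and the index, and reported on its own. Overall then uses nine items and the index runs 0-9.

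Apply the same item set and direction to Overall, the index and the red/green test, and refer to that definition in the Power section and Table 3. Record the choice before acceptability data are analysed.

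The cost is one footnote and one scoring line. The survey items, the data collected and N = 40 do not change.

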**Adherence support acceptability**			
	Effectiveness	Percentage of participants who report it was helpful to receive text reminders Percentage of participants who report it was helpful to complete an action plan	
	Burden	Percentage of participants who report they received too many SMS text messages	

^a^Program acceptability indicators will be operationalized as the percentage of participants who completed the module or program and agreed or strongly agreed with the indicator statement. Some indicators will be asked both in reference to specific modules and in reference to the program as a whole.

^b^We will also create a continuous program acceptability index score for each mother and teenager by summing across acceptability indicators (range 0-9).

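### Table 2 lists ten acceptability indicators but gives the index a 0–9 range, and the focal acceptability rate built on the same set names no unit (mother, teenager, both or dyad)

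*Protocol article*

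**What the plan says.** Table 2 of the protocol article (Methods, Acceptability) lists the program statements by domain: two each for affective attitude, burden and effectiveness, and one each for ethicality, cohesiveness, self-efficacy and opportunity cost. All carry footnote a, which scores an indicator by whether a completer agreed or strongly agreed with it.

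The burden row reads "The module or program was easy to do^a^ The module or program was too long^a" (the raised letters are footnote marks). One effectiveness item reads "The program will reduce my teen’s chances of experiencing dating abuse".

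Footnote b adds a summed index: "We will also create a continuous program acceptability index score for each mother and teenager by summing across acceptability indicators (range 0-9"). The Overall row of Table 2 is defined as "Percentage of participants who report agreement with all acceptability indicators".

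The Power section makes overall acceptability one of the focal outcomes for progression to the main trial, with a red-zone upper limit of 0.55 and a green-zone lower limit of 0.75. Table 3 describes it as the "percentage of those completing the program who agree or strongly that the program is acceptable across all domains" and gives N=40.

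**The concern.** Three things about the indicator set do not fit together.

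- **The count.** Ten listed yes/no indicators cannot give a 0–9 range unless one is left out, and no omission is stated.
- **The respondent.** One index and one range are given to mothers and teenagers alike, but a teenager cannot answer the item about a parent's own teenager as worded.
- **The direction.** Agreeing that the program was too long is unfavourable. With no reverse coding stated, a literal reading of agreement with all indicators requires that complaint, and the sum mixes favourable and unfavourable answers.

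The summed index drives no decision. The all-indicators percentage does, because it is a traffic-light criterion, and it rests on the same unsettled set. It also has no stated unit. The Participants section uses the word participants for mothers; the Incentives section uses it for mothers and teenagers; Table 3 refers only to those completing the program. Teenager appeal is one of the stated reasons for the web version, and acceptability is defined by what both mothers and teenagers think. A criterion that could be met on the mothers' answers would miss part of what it is meant to judge. A criterion whose items and unit are open can also be settled after the data are seen.

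**Working it through.** **1. Range of the index.** Inputs: Table 2, with footnote a scoring each item 0 or 1.

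- Count: 2+2+2+1+1+1+1 = 10, so the sum runs 0–10. The stated 0–9 is not reproduced.
- Other scorings also fail. Seven domains give 0–7; ten five-point items give 10–50 or 0–40.
- Reverse-coding the negative item changes its direction, not the count.
- If only teenagers omit the mother-worded item, mothers have 0–10 and teenagers 0–9. A common 0–9 needs one item dropped for everyone.

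**2. The plan's N=40.** Inputs from the Power section: p0 = 0.55, p1 = 0.75, one-sided α = 0.05, power 0.80, normal approximation with continuity correction.

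- n = [(1.645·√(0.55·0.45) + 0.842·√(0.75·0.25)) / 0.20]² = 34.97
- With correction: (n/4)·[1 + √(1 + 2/(n·0.20))]² = 39.8, rounded up to 40. This agrees with Table 3.

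**3. Exact test per informant.** The red zone is rejected at the smallest count r with P(X ≥ r | 0.55) ≤ 0.05.

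| Completers | Rule | Exact α | Power at 75% |
|---|---|---|---|
| 40 | ≥28 | 0.039 | 0.82 |
| 50 | ≥34 | 0.043 | 0.90 |

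The 50 assumes that half of 100 enrolled dyads complete the program, which is the green limit for completion.

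**4. What combining would do.** Assumptions, none stated in the article: 40 completing dyads, mothers and teenagers combined 1:1, independent answers. The rule for 80 people is then ≥52 (65%), with exact α 0.045.

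- Assumed true rates: mothers 95%, teenagers 55%. The average is (95+55)/2 = 75%, the green limit, while teenagers sit at the red limit.
- Combined test: P(reject red) = 0.99. Teenagers alone (≥28 of 40): 0.04.
- An observed combined rate of at least 75% has probability 0.56, so ruling out red is near certain and landing in green is about even.
- The rule of 52 can be met with 40 of 40 mothers and 52 − 40 = 12 of 40 teenagers (30%).

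**5. Requiring both informants to reject red.** Under independence, with both true rates at 75%:

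- 40 each: 0.82 × 0.82 = 0.67
- 50 each: 0.90 × 0.90 = 0.81

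**The case against.** The strongest reply is that the article never says the two respondents are combined. It keeps them apart elsewhere: separate module surveys, program completion surveys for both, an index for each person, and a sample counted in dyads. If the unit were the dyad, with both members required to agree, low teenager acceptability could not be hidden. This stands. A reader might infer that the go/no-go rate is a pooled percentage, but the text supports only that its unit is not named. The figures in step 4 are therefore conditional.

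A reader might also infer that the combined rate cannot exceed 50%, because teenagers cannot endorse the mother-worded item. That needs combining, no teenager version of the item, and blanks counted as disagreement. None of these is stated, and a questionnaire not shown may hold a teenager wording.

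Nor is 0–9 necessarily a wrong number. Dropping the negative item or the mother-worded item for everyone would produce it. What is established is an unexplained one-item mismatch between table and footnote.

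Finally, the summed index feeds no progression rule, and no comparison of mothers' with teenagers' index scores is planned. This too stands, and the footnote alone would be minor. It does not remove the point, because the focal percentage uses the same indicator list and inherits the same gaps in items, direction and unit.

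**Conclusion.** The point holds in a limited form. Ten indicators are listed against a 0–9 range; one item fits only mothers as worded; one is negative with no stated scoring direction. These are inconsistencies in the printed table and need no assumption. The focal all-indicators rate depends on the same set and has no named unit.

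How much the missing unit matters depends on a reading the article does not fix. If mothers and teenagers were combined 1:1, teenagers at the red limit could be masked (0.99 against 0.04 in step 4, given 40 dyads and independence). A mothers-only rate would not show teenagers' views at all. A both-must-agree dyad rate would avoid the problem.

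It would be tempting to add that green should require both informants and that the stated power is kept. It is kept for each test taken separately, but not for the joint rule, whose power is about 0.67 at 40 each. The correction is worth making before analysis because it concerns a progression criterion.

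**What to change.** 1. In Table 2, either correct the range to 0–10 or name the omitted indicator and use the same set in the Overall row.
2. List the items for each respondent with scoring direction and range: reverse-code the item on length, and either give the teenager wording of the mother-worded item or exclude it for teenagers.
3. In Table 2 and Table 3, define the unit and denominator of the overall acceptability rate. Report it separately for mothers and for teenagers against 55%/75%.

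The cost is wording and one extra results line. Table 3's N=40 then applies to each informant and keeps the planned 80% power for each test, provided that at least 40 of the 100 dyads complete.

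Whether both must be green is a design choice, not a correction. If the sponsor adopts that rule, it should state the joint power: about 0.67 at 40 each and 0.81 at 50 each under independence. The first figure is below the protocol's own 80% standard.
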